## 9.2 Statistical Analysis

The analyses must account for clustering of the data, unless the only comparisons are of cluster means or proportions, using clinic as the unit of analysis. For most outcomes we will perform such an analysis first, using standard t-tests or, where the observations per clinic vary, t-tests weighted by cluster-size. However, relative to individual level analysis this approach is limited by low power (low number of clusters); inflexibility in adjusting for baseline individual level covariates; and inability to model direct impacts of patient characteristics and their interactions with treatment. Therefore we will use regression methods on individual level data for most analyses, and the discussion below is largely restricted to these approaches. While such methods can directly model correlations among units in a cluster (random effects or multilevel models) or more simply adjust standard errors for clustering (GEE, robust standard errors), these approaches are not reliable when number of clusters is small: reliably estimating the ICC to adjust standard errors typically requires 20 or more clusters. Hence, we'll use standard regression methods, but rather than attempt to estimate ICC directly, we will explore the sensitivity of significance levels and conclusions to a range of plausible ICCs values for the outcomes.

AIMs 1a: Depression Treatment Uptake: We'll use logistic regression to compare the proportions of depressed patients (according to PHQ-2) receiving depression treatment in task-shifting vs. control arms. We expect that most patients whose PHQ-2 screen is followed up with a formal evaluation and diagnosis of depression will be prescribed antidepressants, so we are not examining this variable separately from treatment uptake; also, it would be difficult to ascertain if the doctor performed a formal evaluation in the standard arm. The treatment uptake outcome will be estimated using covariates to adjust for baseline characteristics such as age, sex, and physical health. We will add interactions of these covariates with study arm to assess which types of patients are likely to be diagnosed and treated in the task-shifting vs. standard models. For example, it is possible that nurses, who are largely female, are more likely to recognize and treat depression in female clients.

AIM 1b: Change in Depression (treatment response): The effect of task-shifting on treatment response (change in PHQ-9) will be examined using an ITT approach and the whole sample. We will use a repeated-measures, mixed-model approach allowing for correlation of errors over time for an individual (for which the sample size of our individual level data is adequate). The model has the following form:

$$(1) \text{Depression}_{it} = \alpha + \beta(\text{treatment model})_i + \gamma(t) + \delta(\text{treatment model})_i(t) + \theta_i + \varepsilon_{it}$$

Where *t* is time period,  $\beta$  controls for baseline differences between the two,  $\gamma$  is the trend in the outcome common to both groups, and  $\delta$  is the interaction of treatment model with time and shows the intervention effect (task-shifting relative to the control).  $\theta_i$  is an individual random effect and  $\varepsilon_{it}$  idiosyncratic period specific error. A vector of individual level covariates  $X_i$  will be added to estimate the effects of patient characteristics and interactions of  $X_i$  and task-shifting will be used to test for moderators: e.g., do effects of the task shifting model vary by the patient's physical health at baseline? As this is ITT, the estimates will capture the average benefit for depressed PLHA, including those who do and do not receive antidepressant treatment.

To assess effects on those receiving antidepressants, we will estimate (1) on the sample of those treated in both arms; however, randomization does not ensure equivalence of the two groups, since the process of selection into diagnosis and treatment will likely differ. In particular we might expect more seriously depressed patients to be treated in the standard arm. This can be addressed by including baseline PHQ-9 in the regression, or with fewer parametric assumptions, using propensity score matching to match similar patients in control and treatment arms. As both approaches assume that observables fully control for differences across arms in relevant characteristics of treated patients, more caution will be needed in interpretation of the results.

**AIM 2: Assess relationship of depression and public health and economic outcomes:** We will first examine correlates of baseline depression (PHQ-9) including ART adherence, condom use, and work activity. Multi-variate analysis will take advantage of repeated observations per individual to model the effect of changes in depression on changes in these outcomes (individual fixed effects), controlling for unmeasured individual characteristics that may affect both depression and the outcomes. However, it does not control for simultaneity (e.g., change in work status leads to lower depression). With 3 time-points, instrumental variables approaches combined with fixed effects potentially can deal with this problem, using baseline depression to predict change in depression from month 6 to 12, if baseline depression is strongly correlated with change in depression over time. The fixed effects model will also indicate important time patterns in depression and the other outcomes.

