## STUDY OVERVIEW

**DESIGN:** A comparative trial that compares two implementation models for integrating antidepressant treatment into HIV care within 10 health care facilities in Uganda. Using a cluster randomization, 5 clinics are assigned to implement a protocolized model, and 5 others rely on the clinical acumen of trained providers. To evaluate the models, data will be collected from documentation mechanisms integrated into routine care, and from random samples of 100-150 patients enrolled at each site that screen positive for possible depression and are followed for 12 months. A cohort of providers will also be enrolled at each site and followed over 24 months. We will compare the two models on uptake of antidepressant treatment, and change in depression (treatment response), as well as other quality of care outcomes.

**STUDY SITES:** Of the 10 healthcare facilities participating in the study, eight are run by the Ministry of Health and two are private, faith-based, not-for-profit healthcare facilities; two are district hospitals and the others are designated as health centre III or IV facilities by the Uganda Ministry of Health, and are located in the districts of Mpigi, Mityana, Luweero, and Wakiso.

**SAMPLE SIZE:** 10 clusters (clinics), with 100-150 patients at each clinic.

**POPULATION:** Over the course of 12 months at each site, research coordinators (Masters level graduates with social science training) will recruit random samples of 100-150 patients who the triage personnel screen as positive for potential depression (PHQ-2 > 2), who are confirmed to be positive in the research coordinator's own PHQ-2 administration, and who are determined to be medically stable.

**STRATIFICATION:** To ensure the two study arms are balanced on size of clientele (small clinics serve 300-1000 clients, while larger clinics serve 1500-3000 clients), which could influence depression care processes, randomization will be conducted within pairs of clinics that were matched on this variable.

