## 3.0 STUDY DESIGN

INDEPTH-Uganda is a comparative trial that compares two active task-shifting implementation models for integrating antidepressant treatment into HIV care within 10 health care facilities in Uganda. Using a cluster randomization, 5 clinics are assigned to implement a protocolized model, and 5 others rely on the clinical acumen of trained providers. To evaluate the models, data will be collected from documentation mechanisms integrated into routine care, and from random samples of 100-150 patients enrolled at each site that screen positive for possible depression and are followed for 12 months. We will compare the two models on uptake of antidepressant treatment, and change in depression (treatment response), as well as other quality of care outcomes.

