## 9.0 STATISTICAL ANALYSES

**9.1 Power analysis for primary aims.** With 10 clusters, this study is powered to detect medium to large effect sizes; nonetheless, the results will be among the first of their kind, hence informative for subsequent analysis and policy. We calculated detectable differences for different intracluster correlation coefficient (ICC) values. Data from developing countries indicate low correlations of health outcome variables within primary care settings (improving power), including .03 for depression in a collaborative care trial in India, and .011 for maternal/perinatal health outcomes in 8 Latin American countries. ICC tends to be higher for process related measures (which would include the focus of Aim 1a): median=.16 for the same 8 country study.

**Aim 1a (treatment uptake):** With 150 patients per site and assuming 30% antidepressant uptake in the standard model and ICC=.16, we will be able to detect an increase of 28% in uptake rates between the task-shifting and standard clinics ( $\alpha = .05$ , 80% power; one sided test). For ICC=.25 the increase is 34%. Given the systematic procedural difference in the two arms, we expect the actual difference may exceed these amounts.

**Aim 1b (depression change):** For measuring change in PHQ-9 in an intention to treat (ITT) analysis using the whole sample, with ICC =.025, s.d. =3.9 (from our current study), and 10% attrition, we'll have power to detect a 1.26 difference on the PHQ-9 ( $\alpha = .05$ , 80% power; 2-sided

test); for ICC=.01 and .05, detectable differences are .92 and 1.71. For analysis of those receiving antidepressants, we estimate 30% (n=45) of the standard arm patients will be treated (a larger share is expected in the task-shifting arm, which will improve power). With ICCs =.01, .025, and .05 (s.d. = 3.0), and 10% attrition, we will be able to detect changes of 1.00, 1.20, and 1.46 in the PHQ-9. These correspond to medium effect sizes (Cohen's *d*) of 0.33, 0.40 and 0.49.

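### The individual-level models for Aims 1a and 1b contain no clinic term, and no rule says which assumed ICC or which analysis decides, so type I error is not controlled for either primary outcome

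*Protocol*

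**What the plan says.** Section 3.0 sets the unit of randomisation: "Using a cluster randomization, 5 clinics are assigned to implement a protocolized model, and 5 others rely on the clinical acumen of trained providers". The Study Overview gives the size as "10 clusters (clinics), with 100-150 patients at each clinic" and says randomisation was within pairs of clinics matched on clientele size.

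Section 9.2 opens by requiring that clustering be accounted for unless clinics themselves are the unit of analysis. It then takes these steps:

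- Clinic-level t-tests, weighted where clinic sizes vary, are to be done first for most outcomes.
- These are judged inadequate for three reasons. The first is power: "relative to individual level analysis this approach is limited by low power (low number of clusters"). The others are that individual covariates are hard to adjust for, and that patient characteristics and their interactions with arm cannot be modelled.
- The conclusion is: "Therefore we will use regression methods on individual level data for most analyses".
- Random effects, GEE and robust standard errors for clinic are rejected because ten clusters are too few. Instead: "Hence, we'll use standard regression methods, but rather than attempt to estimate ICC directly, we will explore the sensitivity of significance levels and conclusions" over plausible ICC values.

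For Aim 1a the model is a logistic regression with arm, patient covariates and their interactions. For Aim 1b it is equation (1), with arm, time, arm-by-time, a term θ that "is an individual random effect and" a residual error. No clinic or clinic-by-time term appears in either.

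**The concern.** The arm effect is a comparison of five clinics with five clinics. A model with no term for clinic computes its standard error as though the information came from over a thousand separately randomised patients. Its nominal p-value is therefore too small whenever outcomes vary between clinics.

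Section 9.2 recognises this, but its remedy has no anchor. Significance is to be explored over a range of ICCs, with neither the range nor a deciding value given. The clinic-level t-test would be valid, but it is promised only for most outcomes, without naming Aims 1a and 1b, and is then passed over in favour of the regressions. If the two analyses disagree, or the answer changes across the ICC range, the plan does not say what the trial concludes. One care model could then be declared superior because of ordinary clinic-to-clinic variation, or because of an ICC chosen after the data are seen.

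**Working it through.** **Inputs (Section 9.1 unless noted).** Five clinics per arm (Section 3.0). Aim 1a: "With 150 patients per site and assuming 30% antidepressant uptake in the standard model and ICC=.16", one-sided α = .05, with .25 as a second ICC. Aim 1b: SD 3.9, ICC .01, .025 and .05, two-sided α = .05, and 10% attrition, so 150 × 0.9 = 135 per clinic.

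**Design effect.** DE = 1 + (m − 1) × ICC.

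**The plan's own figures first.** For Aim 1b the detectable difference is (1.96 + 0.84) × 3.9 × √(2 × DE / 675), where 675 = 5 × 135. This gives 0.91, 1.24 and 1.65, against .92, 1.26 and 1.71 stated. The first two agree closely and the third is slightly conservative in the protocol. So Section 9.1 applies a design effect to PHQ-9 change, which equation (1) does not do.

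For Aim 1a the protocol states: "we will be able to detect an increase of 28% in uptake rates between the task-shifting and standard clinics". With n = 750 / 24.84 = 30.2 effective patients per arm, the usual two-proportion formulas give 30.3 to 31.3 points (29.3 using the control-arm variance only). The stated 28 is not reproduced. That is a separate matter and does not affect the calculations below.

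**Type I error if no correction is made.** Two-sided: 2 × [1 − Φ(1.96/√DE)]. One-sided: 1 − Φ(1.645/√DE).

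| Outcome | m | ICC | DE | One-sided | Two-sided |
|---|---|---|---|---|---|
| Uptake | 150 | .16 | 24.84 | 37.1% | 69.4% |
| Uptake | 100 | .16 | 16.84 | 34.4% | 63.3% |
| Uptake | 150 | .25 | 38.25 | 39.5% | 75.1% |
| PHQ-9 change | 135 | .01 | 2.34 | – | 20.0% |
| PHQ-9 change | 135 | .025 | 4.35 | – | 34.7% |
| PHQ-9 change | 135 | .05 | 7.70 | – | 48.0% |

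For example, uptake at ICC .16: √24.84 = 4.98, 1.645/4.98 = 0.330, and 1 − Φ(0.330) = 37.1%.

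Simulation with 100,000 trials per setting agrees. Uptake at ICC .16 and m = 150 gave 37.3% one-sided and 70.1% two-sided; PHQ-9 gave 20.0%, 34.8% and 48.1%. In the same simulations the unweighted t-test on ten clinic values (8 df) held 4.9% to 5.2% for uptake and 5.0% for PHQ-9.

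**Type I error if an ICC is assumed and is wrong.** Two-sided: 2 × [1 − Φ(1.96 × √(DE assumed / DE true))].

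- Uptake, m = 150, .16 assumed and .25 true: √(24.84/38.25) = 0.806, giving 11.4% (one-sided, 1 − Φ(1.645 × 0.806) = 9.2%).
- PHQ-9, m = 135, .025 assumed and .05 true: √(4.35/7.70) = 0.752, giving 14.1% (14.3% with m = 150).
- The reverse errors are conservative: .25 assumed and .16 true gives 1.5%; .05 assumed and .025 true (m = 135) gives 0.9%.

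**Why an unanchored range cannot decide.** Suppose the observed PHQ-9 difference is 1.0 point. The standard error 3.9 × √(2 × DE/675) is 0.325, 0.443 and 0.589 at ICC .01, .025 and .05. The z values are 3.08, 2.26 and 1.70, and the two-sided p-values .002, .024 and .090. The same data are significant or not according to an ICC that the plan does not fix.

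**The case against.** A reader might infer that the plan simply treats patients as independent, with a false-positive rate of about 70%. The protocol does not support that. Section 9.2 states that clustering must be accounted for, plans clinic-level t-tests, and re-examines significance across ICCs; nowhere does it say that the uncorrected p-value is the result. Nor is 70% the applicable figure for uptake: Section 9.1 states a one-sided test for Aim 1a, where the uncorrected rate is about 37% and cannot exceed 50%. The sidedness appears only in the power section, so the two-sided 69% is worth reporting only as a conditional figure.

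A reader might also infer that the plan's appeal to power is mistaken. That too goes too far. A regression corrected with an external ICC that happens to be right does have more power than a t-test on 8 df. At a difference of 1.26, ICC .025, SD 3.9 and m = 135, power is 81% with a fixed ICC and normal reference, against 70% with the t-test. The gain is real if the ICC is right; with no correction it is false precision.

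Two further points stand. Requiring significance over the whole range would control error if the true ICC lay within it, so the gap is a missing rule, not a method bound to fail. And in equation (1) a clinic effect constant over time cancels from the arm-by-time contrast, so the PHQ-9 figures need the ICCs to apply to change, which is how Section 9.1 uses them.

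A statistical analysis plan, not shown, might settle which ICC governs. But the protocol itself writes out the Aim 1b model without clinic, specifies the Aim 1a regression without naming one, and turns away from the clinic-level test. That is a choice fixed here, not a detail left open.

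**Conclusion.** The point holds in this form: the individual-level models for both primary outcomes omit the randomised unit, and the only correction offered is an exploration with no governing ICC and no rule on which analysis prevails. Followed as written, Section 9.2 does not control type I error for Aim 1a or 1b.

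The consequence depends on what is finally reported. With uncorrected p-values, error is about seven times nominal for uptake (37% against 5%, one-sided) and four to ten times for PHQ-9 change (20% to 48%). With a correction at too low an ICC it is roughly two to three times nominal. With a correct or conservative ICC, or the clinic-level test, there is no inflation.

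These figures assume equal clinic sizes, ignore the matched pairs, and take the Section 9.1 ICCs to apply to the outcomes analysed. Because both primary outcomes are affected and the remedy is cheap, this should be corrected before the analysis.

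**What to change.** Revise Section 9.2 as follows.

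1. Name the clinic-level comparison, already planned, as confirmatory for Aims 1a and 1b. Use clinic means or, to meet the covariate objection, a two-stage analysis: regress the outcome (PHQ-9 change for Aim 1b) on patient covariates without arm, average the residuals by clinic, and compare five with five by a t-test on 8 df, or 7 df if the clinic-size stratum used for matching is included.
2. State how the matched pairs are handled. A fully paired analysis would leave 5 − 1 = 4 df, so the choice should be made in advance.
3. As an alternative, allow a mixed model with a clinic random effect (clinic-by-time for equation (1)) and small-sample degrees of freedom such as Kenward-Roger. That correction is needed to answer the protocol's own concern about few clusters.
4. Keep the regressions without clinic, the covariate-by-arm interactions and the ICC sensitivity as exploratory. This preserves the protocol's third reason for individual-level modelling.

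The cost is rewording only, with no new data. P-values become less favourable and intervals wider, and power at the stated Aim 1b difference of 1.26 falls from about 81% to about 70%.

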**Longitudinal client cohort:** The client research participants will be assessed at baseline and months 6 and 12. The surveys will be administered by the research coordinator using computer assisted personal interview technology, and will include the PHQ-9 (to independently assess the presence of depression) as well as measures of demographic and background characteristics,

work activity, clinical appointment and ART adherence, quality of life, sexual behavior and measures of psychosocial functioning. All measures have been used successfully in our prior research in Uganda and have been translated into Luganda, the primary native language used in the study setting. Participants will receive 10,000 Ush (~\$4 USD) for each assessment.

**Longitudinal provider cohort:** The provider cohort will be surveyed at the start of intervention implementation and then at months 6, 12 and 24. The measures will include perceived competency in providing depression care, quality of depression treatment provided, effects of the treatment model on clinic functioning, provider burden and patient flow, and impact of depression treatment on the patient's quality of life.

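### Aim 1b tests moderators with a covariate-by-arm term, although model (1) defines the intervention effect as arm-by-time; read literally, the test addresses the wrong coefficient

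*Protocol*

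**What the plan says.** Protocol section 9.2, Aim 1b, writes a repeated-measures model for PHQ-9 with an arm term (beta), a time term (gamma), an arm-by-time term (delta) and a person-level random effect. It gives each coefficient a role. Beta "controls for baseline differences between the two". Delta "is the interaction of treatment model with time and shows the intervention effect (task-shifting relative to the control").

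A vector of patient covariates is then to be added. The interactions of these covariates with task-shifting "will be used to test for moderators: e.g., do effects of the task shifting model vary by the patient's physical health at baseline". The equation is not rewritten with the covariates in it, and no covariate-by-time or covariate-by-arm-by-time term is mentioned.

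The visit schedule is in section 7.0: "The client research participants will be assessed at baseline and months 6 and 12".

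For Aim 1a the same section uses a logistic model of treatment uptake, "using covariates to adjust for baseline characteristics such as age, sex, and physical health", and continues: "We will add interactions of these covariates with study arm to assess which types of patients are likely to be diagnosed and treated". That model has one outcome per patient and no time term.

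**The concern.** The question asked in Aim 1b is whether the effect of the care model varies with a patient characteristic. By the protocol's own definition the effect is delta, so the question is whether delta depends on X. A product of X and arm alone makes beta depend on X, and the protocol assigns beta to baseline differences. Letting delta depend on X requires the product of X, arm and time.

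The covariate-by-arm form suits Aim 1a, where the arm coefficient is the effect. It does not carry over to model (1), where the arm coefficient is not.

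Two errors could follow. Real moderation would be reported as smaller than it is. And an arm difference in the X–depression relation that was present at enrolment could be reported as a difference in how patients respond.

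**Working it through.** **Inputs from the protocol.** Visits at months 0, 6 and 12 (section 7.0). Five clinics per arm (section 3.0). From section 9.1: 150 patients per site, and for the Aim 1b intention-to-treat calculation "with ICC =.025, s.d. =3.9 (from our current study), and 10% attrition", two-sided alpha .05, 80% power.

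**The plan's own figure.** The protocol gives no figure for the moderator tests. Its detectable main effect is 1.26 PHQ-9 points.
- Patients per clinic after attrition: 150 × 0.9 = 135, so 5 × 135 = 675 per arm.
- Design effect: 1 + 134 × 0.025 = 4.35.
- SE = 3.9 × √(2 × 4.35 / 675) = 0.443.
- Detectable difference = 0.443 × (1.960 + 0.842) = 1.24, against 1.26 stated.

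The figure is reproduced to within 2%, so 675 per arm and SD 3.9 are a fair basis for the illustration below.

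**What the two-way term estimates.** Code time as 0, 1, 2. Let m(t) be the true moderation at visit t, with m(0) = 0 because no treatment effect exists at baseline. Let b be any baseline X-by-arm difference that persists unchanged. X-by-arm is constant within a person, so with complete balanced data and a person random intercept its coefficient is determined by the person means:

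two-way coefficient = b + [m(0) + m(1) + m(2)] / 3

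With month-12 moderation set to 1:
- linear growth: (0 + 0.5 + 1) / 3 = 0.50
- full effect by month 6, then constant: (0 + 1 + 1) / 3 = 0.67
- no moderation, baseline difference b: the coefficient equals b

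**What the three-way term estimates.** With three equally spaced visits the fitted slope is (last − first) / 2. Scaled to month 12 it is m(2) − m(0), which equals 1 for both shapes, and b cancels.

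**Illustration of power and false findings.** Assumptions not in the protocol: standardised covariate, SD 3.9 at each visit, within-person correlation ρ of 0.3 to 0.7, no clinic effect.

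SE of the two-way term = √[3.9² × (1 + 2ρ)/3 × 2/675].
SE of the three-way term scaled to month 12 = √[2 × 3.9² × (1 − ρ) × 2/675].

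At ρ = 0.5 these are 0.173 and 0.212. For a linear moderation of 0.6 points per SD at month 12, the ratios of estimate to SE are 0.30/0.173 = 1.73 and 0.60/0.212 = 2.83, giving power of about 41% and 81%. Simulation with 1,000 runs per scenario agrees:

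| ρ | Two-way power, linear 0.6 | Three-way power, linear 0.6 | Two-way rejection, no moderation, b = 0.5 | Three-way rejection, same case |
|---|---|---|---|---|
| 0.3 | 51% | 65% | 91% | 5% |
| 0.5 | 42% | 83% | 82% | 5% |
| 0.7 | 38% | 95% | 74% | 5% |

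Two limits on this table:
- With no moderation and no baseline difference, both tests rejected in about 5% of runs (4% to 7%).
- The two-way term does not always have less power. With a 1.0-point effect complete by month 6 and ρ = 0.3, it rejected in 99% of runs against 98%, while still estimating 0.67 instead of 1.0.

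**The case against.** The strongest reply is that the faulty model is inferred. The equation is never written out with covariates, the stated question is the correct one, and "task-shifting" could be shorthand for the task-shifting effect, that is, delta. This stands in part: the wording is wrong or ambiguous, and it does not prove that the wrong model would be fitted. However, the same paragraph names the time interaction explicitly when it means the effect, and names only the arm when it describes the moderator test. An analyst following the text would fit the two-way term. This is a stated term in conflict with its own model, not a detail left to a statistical analysis plan.

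A second reply is that the false-finding rates depend on an assumed baseline difference. This also stands. At the individual level the SE of the baseline X-by-arm difference is 3.9 × √(2/675) = 0.212, so a gap of 0.5 is about 2.4 SE and would arise by chance in about 2% of trials. The protocol gives no evidence that such a gap exists. What makes one conceivable is the design: ten randomised clinics, and patients told of the study by providers trained separately by arm (sections 5.1 and 6.3). The calculation ignores clinics, so it cannot say how often this would happen.

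A reader might go further in three ways that the document does not support:
- **That moderators are simply halved.** One half holds only for linear growth; a full effect by month 6 keeps two thirds. The protocol fixes neither the shape of the effect nor the coding of time.
- **That the Aim 1a interactions share the fault.** They do not. Uptake is a single outcome with no time term, so covariate-by-arm is the right term there.
- **That the interactions form an uncontrolled family of tests.** The protocol does not count them: Aim 1a gives examples of covariates and Aim 1b names only physical health as an example. Exploratory labels and multiplicity rules for secondary interactions commonly belong to a statistical analysis plan, which is not shown. Moderators are not among the aims in section 2.0.

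**Conclusion.** The point holds for the Aim 1b moderator test alone. As written, the interaction modifies the coefficient that the protocol reserves for baseline differences, not the one it calls the intervention effect.

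With complete data at months 0, 6 and 12, the two-way coefficient recovers about one half (linear growth) to two thirds (full effect by month 6) of the month-12 moderation, and it absorbs a constant baseline X-by-arm difference one for one. These factors do not depend on clustering. The power and rejection rates do, and they also rest on an assumed visit SD, within-person correlation and effect size, so they only illustrate the contrast.

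The primary treatment contrast delta is unaffected. This is a correction to a secondary analysis, of minor to moderate importance.

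**What to change.** State in section 9.2 that Aim 1b moderators are tested by the covariate-by-treatment-by-time coefficient, with all lower-order terms in the model, including covariate-by-time and covariate-by-treatment. Writing model (1) out once with these terms would remove the ambiguity. The Aim 1a wording can stay as it is.

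The cost is one sentence and a few model terms, with no new data. When within-person correlation is low, the three-way test can have slightly less power than the two-way test if the effect is complete by month 6; that is the price of estimating the quantity the protocol asks about.

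### In the treated-only analysis, adding baseline PHQ-9 to model (1) as a covariate main effect does not adjust the arm-by-time effect for severity

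*Protocol*

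**What the plan says.** Protocol 9.2, Aim 1b, sets out model (1) for PHQ-9 with an arm term β, a time trend γ, an arm-by-time term δ, and θ, which "is an individual random effect and" is accompanied by a period-specific error. The arm term β "controls for baseline differences between the two" groups, so month 0 belongs to the outcome series. Section 7.0 gives the occasions: "The client research participants will be assessed at baseline and months 6 and 12". The effect of interest is δ, which "is the interaction of treatment model with time and shows the intervention effect (task-shifting relative to the control").

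For patients who receive antidepressants, "we will estimate (1) on the sample of those treated in both arms". The section accepts that randomization does not make these two groups comparable and adds: "In particular we might expect more seriously depressed patients to be treated in the standard arm". It then offers two remedies joined by an or. One is the covariate: "This can be addressed by including baseline PHQ-9 in the regression". The other is propensity score matching, described as needing fewer parametric assumptions. It closes by asking for caution, because both remedies rely on observed characteristics being sufficient.

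Section 9.1 gives this analysis its own power statement, with SD 3.0, 10% attrition and ICCs of .01, .025 and .05: "we will be able to detect changes of 1.00, 1.20, and 1.46 in the PHQ-9".

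**The concern.** The covariate remedy is aimed at a difference in baseline severity, but the reported quantity is a difference in change. In a random-intercept model that already holds month 0 as an outcome, a patient-level constant shifts that patient's level and not the slope. Baseline PHQ-9 would then stand on both sides of the equation and alter only β.

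Two things are at stake. First, the report would claim adjustment for severity that had not reached δ. Secondly, if the standard arm (the clinical acumen arm elsewhere in the protocol) treats patients because their baseline score is high, those patients fall back further towards the mean, and the fall counts as better response in that arm. Matching on baseline would remove this component, so the two remedies offered for one problem can give different answers.

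**Working it through.** **1. The plan's own figure.** Inputs from 9.1: 45 treated per standard-arm clinic, 10% attrition (m = 45 × 0.9 = 40.5), 5 clinics per arm, SD 3.0. Alpha .05 two-sided and 80% power are stated for the intention-to-treat figure and assumed here. Detectable difference = SD × √[2(1 + (m − 1)ICC)/(5m)] × (1.960 + 0.842).

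| ICC | Computed | Stated |
|---|---|---|
| .01 | 0.99 | 1.00 |
| .025 | 1.18 | 1.20 |
| .05 | 1.44 | 1.46 |

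These agree within 2% and are not in dispute. They give a yardstick for the bias.

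**2. Why δ does not move.** With visits at 0, 6 and 12 months and none missing, the fitted linear slope for a patient is (Y12 − Y0)/12 per month. In the random-intercept model, δ is the arm difference in the mean of these slopes. A main effect of baseline PHQ-9 adds the same constant to Y0, Y6 and Y12 and cancels from every slope.

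**3. Check on simulated data.** No true arm effect; 2000 treated patients per arm; standard arm selected on observed baseline above 14, the other above 10; stable-trait SD 2.5, period-error SD 3.0 (all assumed). Positive values favour the standard arm; δ is per 6-month period.

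| Model | δ, complete | δ, 10% of follow-up missing |
|---|---|---|
| (1) as written | 0.830 | 0.709 |
| plus baseline PHQ-9 | 0.830 | 0.703 |
| plus baseline PHQ-9 × time | 0.119 | −0.073 |

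The first two complete-data values agree to six decimals. Only the arm main effect changed, from −2.36 to −0.80. With time as categories, the month-12 contrast was 1.661 with or without the covariate. With complete data, matching 1:1 on baseline gave δ = 0.094, and month-12 analysis of covariance gave an arm difference of 0.239 points (SE 0.126).

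In other simulations with about 10% missing at month 12, the 12-month difference went from 1.177 to 1.165 in one and, in the largest shift seen, from 1.00 to 0.88 in another; baseline × time brought the latter to 0.11.

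**4. Size if treatment tracks the observed baseline score.** The plan gives 30% uptake for the standard arm. The 58% is an assumption: 30% plus the 28-point detectable increase in 9.1. Correlation r between baseline PHQ-9 and being treated (.3 to 1.0) and correlation ρ between baseline and month 12 (.3 to .5) are also assumptions.

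- Mean elevation among a treated fraction p, in SD units at r = 1, is φ(z)/p: 1.159 for 30% and 0.674 for 58%; difference 0.485.
- Baseline gap = SD × r × 0.485. Bias in 12-month change = gap × (1 − ρ).

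| SD | Baseline gap, r = .3 to 1.0 | Smallest bias (r = .3, ρ = .5) | Largest bias (r = 1.0, ρ = .3) |
|---|---|---|---|
| 3.9 | 0.57 to 1.89 | 0.57 × 0.5 = 0.28 | 1.89 × 0.7 = 1.32 |
| 3.0 | 0.44 to 1.46 | 0.44 × 0.5 = 0.22 | 1.46 × 0.7 = 1.02 |

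The bias favours the standard arm. The 3.9 is the plan's intention-to-treat SD; 3.0 is its treated-only SD.

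**5. Size if treatment tracks stable severity.** Same inputs at SD 3.9, with selection on the part of the score that persists. The arm difference in change was 0.00 to within about 0.02. Month-12 analysis of covariance on baseline was off by 0.2 (r = .3) to 1.0 (r = 1.0) points, now in favour of task-shifting.

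**The case against.** The protocol does not say that baseline PHQ-9 enters as a main effect, and covariate form is often left to the analysis plan. That softens the point without removing it. The text says that model (1) is what is fitted, names δ as the effect, keeps month 0 in the outcome, and mentions no baseline-by-time term. Read plainly, the stated remedy does not work. If analysis of covariance was intended, one sentence settles it.

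A reader might infer that the treated-only result is bound to favour the standard arm. The documents do not support that. The random effect and the arm term already absorb stable severity differences; bias in δ needs selection on the transient part of the observed score. The mechanism is not settled: treatment in the clinical acumen arm rests on provider judgment (6.2), and the survey PHQ-9 is an independent assessment (7.0) that is nevertheless shared with providers (11.2). This objection stands, and it means that conditioning on baseline is not automatically the better answer.

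A reader might also take 0.3 to 1.3 points as following from the plan's own inputs. It does not: 58% is a detectable uptake, not an assumed one; SD 3.9 belongs to the intention-to-treat calculation; and the top of the range needs severity alone to decide treatment.

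Finally, the section already urges caution and offers matching. Matching that includes baseline PHQ-9 would balance observed severity. The caution, however, concerns what observables miss, whereas baseline severity is observed and the covariate route still leaves it unadjusted in δ.

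**Conclusion.** The stated remedy does not adjust the stated effect. That δ is invariant to a baseline main effect is algebra for complete data and needs no assumption about patients; with about 10% missing the shift was small beside the effect of a baseline-by-time term.

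The consequence for the estimate is conditional. If selection follows the observed score, the remaining bias is about 0.2 to 1.0 points over 12 months at the plan's treated-only SD (0.3 to 1.3 at SD 3.9) in favour of the standard arm. At the upper end that is about the smallest change the plan says it can detect. If selection follows stable severity, the unadjusted δ is unbiased and baseline conditioning errs by about 0.2 to 1.0 points (SD 3.9) the other way.

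Severity is moderate. This is a subsidiary analysis of a post-randomization subset, it is already flagged for careful interpretation, and the whole-sample intention-to-treat analysis of Aim 1b is not touched.

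**What to change.** In 9.2, or in the analysis plan, replace the sentence on baseline PHQ-9 with one of these for the treated-only analysis:

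- PHQ-9 at months 6 and 12 is the outcome, with baseline PHQ-9 by visit as covariate, and the effect is the arm contrast at month 12. With month 0 out of the outcome, the arm-by-time coefficient is no longer that effect, so the contrast has to be named.
- Month 0 stays in the outcome and baseline PHQ-9 × time is added; the effect remains δ.

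Report the unadjusted δ alongside as a sensitivity analysis, and state that the two rest on different assumptions about why patients were treated. Agreement would be reassuring; disagreement should be shown and not resolved by choosing one. The cost is a sentence or two and one extra model fit, with no new data.
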